### Analysis

#### Quantitative analysis

We will use different methods to evaluate the effectiveness of the QUALI-DEC intervention [13, 14]. For the primary outcome, interrupted time series analysis (ITSA) based on segmented regression will estimate the mean changes in the level (immediate change) and trend (sustained change) of monthly CS rates across all participating hospitals in relation to their baseline level and pre-existing trend. We will follow the quality criteria proposed by Ramsay et al. for our ITSA to ensure that our study is adequately reported [35]. For secondary outcomes, we will use a before and after cross-sectional design that will include medical records and women’s interviews. We will compare the outcomes between the two periods of the cross-sectional survey, adjusting for hospital and woman characteristics, to evaluate changes in satisfaction with the birth experience, breastfeeding and medical practices, and maternal/perinatal morbidity. For implementation outcomes, checklist ratings during monitoring visits will be used to compute average scores of the fidelity, dose, and reach of the intervention. Parametric tests will be used to assess changes over time for each facility and differences between study sites.

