### Targeted sites and participants

The study will be conducted from January 2020 to December 2024, in 32 healthcare facilities (8 per country) with high CS rates. Facilities were selected purposely with country investigators to reflect the range of contexts, such as secondary and tertiary levels of care, public and private hospitals, and teaching and nonacademic facilities (Table 4). The intervention directly targets healthcare providers involved in obstetric care and all women who give birth in the participating hospitals during the study period. We have defined providers as obstetricians and nurses/midwives working in the maternity ward in the study facilities. Women will be eligible if they give birth to a newborn (birthweight ≥ 500 g in Argentina and Vietnam or ≥ 1000 g in Burkina Faso and Thailand), alive or dead, and with or without malformations. The intervention does not target patients admitted for abortion or miscarriage or those who delivered at home or in another facility that is not a participating hospital.

**Table 4 Tab4:** Characteristics of participating hospitals by country

Characteristic	Argentina	Burkina Faso	Thailand	Vietnam
Type of hospital				
Public without private ward	8	8	0	2
Public with private wards	0	0	8	4
Private	0	0	0	2
Level of reference				
Tertiary	4	2	6	2
Secondary	4	4	2	4
Primary	0	2	0	2
Teaching hospital				
Yes	8	3	8	4
No	0	5	0	4
Type of medical records				
Electronic	8	0	4	1
Paper-based	0	8	4	7
Range of annual births	1200-5600	2500-6000	2500-7500	2800-42,000
Range of CS rates	23-38%	21-48%	36-56%	23-54%

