### Implementation strategy

The implementation strategy is aligned within the usual model of care in participating healthcare facilities. The main implementers are the local OLs and healthcare providers who are involved in the program and are supported by the country-level study coordinator. Formative research in the baseline period will assess the main drivers and barriers, and a meeting will be held among all stakeholders to discuss implementation issues. Parliamentarians and representatives of women’s associations will be involved in this meeting to consider women’s views. Then, the intervention will be introduced in each country with the 5-day training workshop addressed to OLs. OLs will receive financial incentives during the intervention period to compensate for the loss of revenues related to the decrease in their clinical activities. OL supported by local committee will encourage antenatal care providers to deliver the DAT booklet to eligible pregnant women. This will require a series of on-site meetings in all relevant facilities to inform and motivate providers and to obtain their formal commitment. In addition, a DAT application will be developed for smartphones and made available in the settings in which it is considered culturally appropriate and most acceptable and convenient for women. Posters will be displayed on the wall of the waiting room of antenatal care centers with the QR code to access the web/smartphone application. Other information, educational and communication (IEC) materials, such as flipcharts or posters, will be developed to facilitate the briefing of healthcare providers, companions, and laboring women. These IEC materials will include reminders about the importance of labor companionship, the role of companions, and the regulations of the labor wards. The country-level coordinator will conduct quarterly visits to each participating hospital during the 2-year implementation period to identify further barriers for the implementation process and possible strategies to overcome those barriers, verify data quality and document and report on the study’s progress.

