**Fig. 4 Fig4:**
[figure not shown]
Data collection and analysis methods for process evaluation

To align the intervention and the implementation strategy to the local context, we conduct qualitative research, document review at the country level, and a readiness assessment of each participating facility. The qualitative research will include semi-structured interviews with women, potential companions, and healthcare providers to obtain a comprehensive understanding of the health system and societal context in each country [19]. Additional interviews with policy-makers and representatives of women’s and professional associations (gynecologists-obstetricians and nurses/midwives) will allow us to complete the stakeholder mapping and analysis. Following the context assessment and in consultation with QUALI-DEC developers and implementers, we will define assumptions on what may need to happen (mechanisms of change), and we will hypothesize about how change will happen at the individual level (healthcare providers, women, and companions), at the organizational level (healthcare facility), and through the interaction of participants. Discussions and meetings will be held by video conference with country researchers and during face-to-face meetings with high-level stakeholders and local OLs in each country. To further assess the potential scalability of the intervention within the countries, we will include a participative scalability assessment in the in-country meetings to summarize early opportunities and challenges for scale up [30].

We will construct a theory of change to guide the process evaluation. We will define indicators of fidelity (whether the intervention was delivered as intended), dose (the quantity of intervention implemented), and reach of intervention (whether women and providers came into contact with each relevant component of QUALI-DEC) [15]. These indicators will be measured at the individual and organizational levels in all facilities using quarterly monitoring visits at each hospital and data from the postpartum cross-sectional survey (proportion of women who used the DAT during antenatal care or chose a companion during labor).

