### Sample size

Limited guidance is available on sample size calculation for time series analyses, and many of the recommendations focus on the need for sufficient time points pre- and postintervention to precisely ascertain trends and levels [32, 33]. Our analysis on the primary outcome (monthly CS rates among low-risk women) will include 12 time points preintervention, 24 time points during the intervention phase, and 24 time points during the follow-up phase.

The approach for calculating the required number of participants for the postpartum cross-sectional survey is used for a “before-after” noncontrolled study design. We estimated that a sample of 470 women at baseline and 470 women at the end of the intervention period will ensure 90% statistical power to detect an effect size of 0.3 standard deviations or greater in satisfaction scores with a two-sided 5% significance level [34]. The calculation accounted for the clustered nature of the data by hospitals with a design effect of 2. Allowing for a 20% nonresponse rate, we aim to recruit 564 women in each phase. The proposed sample size (i.e., 564) can be achieved with 2 weeks of data collection in Argentina and Burkina Faso and with 1 week of data collection in Thailand and Vietnam. This sample size will be for each country and will allow to draw conclusions independently for each country and produce individual country interpretations. We estimated that 3980 births will occur during this data collection period in all participating hospitals of the four countries. This overall sample size for the cross-sectional survey will ensure accurate measurements of other secondary outcomes (maternal and perinatal morbidity, time of breastfeeding initiation). Estimations of outcomes at each time point will fluctuate within a 95% confidence interval with the following bounds: 10% rate ± 1% (example: postpartum hemorrhage); 20% rate ± 1.3% (example: second-degree perineal trauma); 40% rate ± 1.5%; (examples: overall CS rate, breastfeeding within 1 h of birth).

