### Subgroup analyses

The integration of quantitative process measures into outcome datasets will contribute to understanding how implementation variability affects outcomes (on-treatment analyses) and to testing hypotheses arising from qualitative analyses. For example, time-series models with multigroup comparisons will enable us to conduct formal statistical tests comparing the level and slope of the primary outcome between different categories of healthcare facilities reflecting different levels of implementation, thereby quantifying the variation of effect size between subgroups [41] and revealing the mechanisms of impact. Additionally, outcomes between women in different socioeconomic categories (in terms of education, place of residence, place of birth, and wealth index) and between periods will be compared to assess the equity of the QUALI-DEC intervention.

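### The subgroup analysis draws a mechanistic conclusion from hospitals grouped by implementation measured during the outcome period; call it associational, and model implementation scores jointly rather than facility by facility

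*Protocol article*

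**What the plan says.** - **Scores and tests** (Quantitative analysis): "checklist ratings during monitoring visits will be used to compute average scores of the fidelity, dose, and reach of the intervention". Then: "Parametric tests will be used to assess changes over time for each facility and differences between study sites". No test is named.
- **Who visits, and how often** (Implementation strategy): "The country-level coordinator will conduct quarterly visits to each participating hospital during the 2-year implementation period". The same role supports the local implementers, looks for ways around barriers and checks data quality.
- **Sources of the indicators** (Process evaluation): they are measured "using quarterly monitoring visits at each hospital and data from the postpartum cross-sectional survey". The survey supplies, for example, the "proportion of women who used the DAT during antenatal care or chose a companion during labor".
- **Hospitals** (Targeted sites and participants): the study runs "in 32 healthcare facilities (8 per country) with high CS rates".
- **Timing** (Outcomes): the monthly cesarean rate covers 12 months before, 24 months during and 24 months after implementation. The postpartum survey is run at baseline and at the end of the intervention period.
- **Use of the scores** (Subgroup analyses): process measures are merged with outcome data for what the article calls on-treatment analyses. The example given is a time-series comparison between "different categories of healthcare facilities reflecting different levels of implementation, thereby quantifying the variation of effect size between subgroups". The same sentence adds that this will bring the intervention's mechanisms to light. No cut-off or time window for forming the categories is given.

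**The concern.** Implementation level is neither randomized nor fixed at baseline. It emerges while the outcome is emerging. Three routes other than a causal effect of implementation could produce a difference in level or slope between categories:

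1. **Confounding.** Leadership, staffing or local policy may drive both good implementation and a falling cesarean rate.
2. **Reverse causation.** Audit feedback shows cesarean rates to staff, and the visiting coordinator also verifies the data. Nothing stated keeps the rating separate from knowledge of the trend, so a hospital whose rate is already falling may be rated as implementing better.
3. **Rater and country.** If each country has its own coordinator, a comparison of sites in different countries cannot separate hospital from rater.

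A type III hybrid design exists mainly to test the implementation strategy, so implementation findings will carry weight with readers. The secondary matter is how the scores are tested: many small separate tests use the data poorly and make isolated significant results hard to interpret.

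**Working it through.** The article gives no power, sample size or error rate for the implementation scores, so there is no stated figure to reproduce.

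**Step 1: order in time.** The outcome phases are 12 + 24 + 24 = 60 months. Numbering them from 1 (my numbering):

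| Months | Outcome | Implementation measure |
|---|---|---|
| 1-12 | baseline level and trend | baseline survey; no implementation visits |
| 13 | immediate level change is estimated here | ratings have barely begun |
| 13-36 | trend during implementation | about 8 quarterly ratings; second survey at the end |
| 37-60 | trend during follow-up | none stated |

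A category built on the whole implementation period is mostly measured after the immediate level change that it is meant to explain, and alongside the implementation-phase trend. Only months 37-60 clearly follow it. Correct order there would still not remove confounding.

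**Step 2: number of ratings.** 4 visits a year x 2 years = about 8 per hospital (derived, not stated). Over 32 hospitals: 32 x 8 = 256 ratings per score.

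**Step 3: multiplicity.** The article states the 5% level ("with a two-sided 5% significance level") only for the survey sample size. I assume it for these tests, and I assume independence between tests.
- One score, 32 hospitals: 1 - 0.95^32 = 0.806. Expected false positives: 32 x 0.05 = 1.6.
- Three scores, 32 x 3 = 96 tests: 1 - 0.95^96 = 0.993. Expected: 96 x 0.05 = 4.8. The three scores within a hospital are probably correlated, so 0.993 is an upper guide.

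**Step 4: serial correlation.** I used 100,000 simulated null series of 8 points with first-order autoregressive errors, tested by an ordinary least-squares slope t-test on 6 degrees of freedom at two-sided 5%. Both the correlations and this naive test are assumptions.

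| Lag-1 correlation | Slope test error | First half vs second half t-test error |
|---|---|---|
| 0 | 5.2% | 5.0% |
| 0.2 | 8.8% | 8.6% |
| 0.3 | 11.4% | 11.2% |
| 0.5 | 18.7% | 17.5% |
| 0.7 | 28.9% | 25.6% |

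With 7 or 9 ratings the slope-test error at correlation 0.5 is 17.3% or 20.1%. Coarse independent ratings keep it at 4.8% to 5.5%. So a short series does not by itself inflate error; ignored correlation does.

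**Step 5: power of one facility's test.** With 8 independent ratings, power is 12%, 35%, 64% and 87% for a total change of 1, 2, 3 and 4 residual standard deviations. The short series mainly costs power.

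**The case against.** The best defense is that the article does not commit to a poor analysis. A parametric test may be a mixed model or a regression with autocorrelated errors. Multiplicity handling, category cut-offs and the grouping window are details that an article may leave to an analysis plan not shown here. The grouped comparison is offered as an example, labelled on-treatment, and placed under subgroup analyses. The primary segmented regression does not use the scores, and in-depth case studies also address how the intervention works.

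Much of this stands, and it rules out several stronger readings that a reader might infer:

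- **That false positives are inherent in the plan.** Not supported. Eight independent ratings hold about 5% error, and the higher figures need an assumed correlation and an assumed naive test. The article also attaches no trial-level claim to the facility tests.
- **That the facility test results define the implementation categories.** Nothing says so; the basis of the categories is not described.
- **That companion reach is computed among all women, and so falls mechanically when more cesareans precede labor.** No denominator is stated. Reach is tied to relevant components, the decision tool is restricted to eligible women, and the companionship model will set its own eligibility criteria.
- **That every indicator rests on eight serial ratings.** Decision-tool use and companion choice come from the survey, which has two time points.

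The article also does not say that site comparisons cross countries, so the rater problem is conditional on that. What the defense does not answer is the stated inference: labelling a comparison on-treatment does not license a conclusion about mechanism.

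**Conclusion.** The point holds as a finding about inference, with a smaller one about efficiency. The Subgroup analyses section draws a mechanistic conclusion from groups defined after the intervention starts, largely over the same 24 months as the outcome. The rating role also supports implementation. Confounding and reverse causation cannot be excluded. Their size cannot be calculated from the document.

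Separate facility tests on about 8 ratings are a weak use of the data even if each is valid: 35% power for a 2-standard-deviation total change, and an 81% chance of at least one false signal over 32 independent 5% tests. The range of about 11% to 29% error per facility applies only at assumed lag-1 correlations of 0.3 to 0.7 that the analysis ignores. The primary effectiveness analysis is not affected.

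**What to change.** 1. **Subgroup analyses.** Describe the comparison by implementation level as exploratory and associational, and remove the claim about mechanism. State the window and rule for forming categories, and form them without sight of cesarean rates. Compare within country, or adjust for country and baseline cesarean rate.
2. **Sensitivity analysis.** Relate first-year scores to cesarean rates from the second implementation year on. This keeps 12 + 24 = 36 of the 48 months after onset. It gives up the immediate level change, and it reduces but does not remove reverse causation, because a first-year fall can raise first-year scores and persist.
3. **Quantitative analysis.** For each visit-based score, replace separate facility tests with one mixed model over all 32 hospitals: random intercept and slope per hospital, a country effect, and allowance for serial correlation. Report facility-level changes as estimates with intervals. Analyze survey-based indicators separately as a two-time-point comparison.

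The cost is slightly more analysis work and a more modest stated conclusion. No new data are needed, and the primary analysis stays as it is.

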#### Qualitative analysis

Qualitative data from observations and IDIs will be analyzed and interpreted using a thematic analysis approach [36]. Interview transcripts will be analyzed in the local language at the country level. Final themes and key quotations will be translated into English for sharing with the researchers of the QUALI-DEC consortium. Framework analysis will be used to provide an in-depth understanding of acceptability [37, 38] by providers and women/companions and the empowerment [39, 40] of both stakeholders to act on CS decision-making. We will define acceptability as the perception of providers and women that the QUALI-DEC intervention is agreeable, entails an acceptable burden, is ethical and economically feasible, and leads to positive outcomes. We aim to understand the extent to which each component of the intervention and its process are both socially and technically accepted in each context. Empowerment can be understood not only as a process but also as an outcome to assess whether the intervention has helped providers and women act on CS decision-making. The analysis will focus on the individual empowerment of women and providers. We anticipate that our intervention will enhance providers’ empowerment by presenting them with monthly statistics promoting reflexivity on their practices, and this increased awareness of clinical practices will, in turn, enhance obstetricians’ and midwives’ sense of agency and self-determination in deciding on interventions during labor and delivery. From the women’s point of view, the study will detail the self-empowerment and professional support provided to women to choose the mode of delivery that better suits their needs. We will analyze the effect of the intervention on women’s self-esteem, knowledge, and sense of empowerment when deciding on the mode of delivery. In our analysis of empowerment, particular attention will be paid to the gender dimension, including the gender dynamics between different categories of providers and between providers and women and how gender norms shape values and decisions related to childbirth.

### Subgroup analyses

The integration of quantitative process measures into outcome datasets will contribute to understanding how implementation variability affects outcomes (on-treatment analyses) and to testing hypotheses arising from qualitative analyses. For example, time-series models with multigroup comparisons will enable us to conduct formal statistical tests comparing the level and slope of the primary outcome between different categories of healthcare facilities reflecting different levels of implementation, thereby quantifying the variation of effect size between subgroups [41] and revealing the mechanisms of impact. Additionally, outcomes between women in different socioeconomic categories (in terms of education, place of residence, place of birth, and wealth index) and between periods will be compared to assess the equity of the QUALI-DEC intervention.

### Knowledge transfer

In consultation with key stakeholders in each participating country, we will develop an innovative evidence-based knowledge transfer strategy [42, 43], adapted to each context. The key ingredients of this strategy will be training, implementation, and evaluation of a knowledge broker in each country who will facilitate the adaptation, dissemination, and exploitation of QUALI-DEC findings by key stakeholders (see Additional files 1, 2 and 3). As the implementation of knowledge brokering is very innovative, it will be the subject of an in-depth evaluation in order to generate knowledge about its processes and effectiveness. A specific research protocol for this part of the QUALI-DEC project will be published later.

## Discussion

There is an urgent need for interventions and implementation strategies that optimize the use of CS while improving health outcomes and satisfaction in LMICs. QUALI-DEC aims to test whether the audit and feedback, decision aid, and patient-centered care approaches supported by local OLs improve the quality of decision-making and perinatal outcomes.

The components of the QUALI-DEC intervention have been tested in randomized controlled trials (RCTs) aiming to reduce the overuse of CS [10]. However, the research reported to date has shown only modest effectiveness in reducing CS rates (Table 1). Evidence on the effect of implementing evidence-based clinical practice guidelines combined with A&F and opinion leaders was available from two RCTS, both from Canada [44, 45]. The effect size on CS rates was moderate to low. However, no research evidence was identified on the acceptability or the impact on equity of this type of intervention. Evidence on the effect of companionship was available from a meta-analysis of 26 RCTS [11]. The effect size on CS rates was moderate. A qualitative evidence synthesis identified various factors affecting successful implementation and sustainability of labor companionship [46]. Three RCTs conducted in the UK [47], Australia [48], and the USA [49] found that decision-support tools improved women’s knowledge and reducing decisional conflict about mode of delivery options, but had variable effects on their uptake of trial of labor or vaginal birth after cesarean section. However, there are no published randomized trials on the effect of decision aids on women without a previous cesarean section. A qualitative evidence synthesis suggests that women welcome new information and learning about childbirth which can mediate pregnant women’s concerns about risk. Women perceive educational interventions and decision-aid tools as a “starting point,” a springboard for seeking more information and for a more meaningful dialog with health professionals [50].

The reasons behind the limited success of nonclinical interventions to reduce unnecessary CS include the failure to acknowledge the multifactorial and complex nature of CS overuse and, accordingly, the failure to design multifaceted interventions. In addition, not enough emphasis has been given to the evaluation of the implementation strategies, which is a critical component underpinning effectiveness, particularly regarding complex and behavioral driven interventions. Our ambition is to implement a multifaceted intervention targeted at women, healthcare professionals, and organizations simultaneously. The study will generate evidence on the feasibility, acceptability, implementation, effectiveness, and equity of this intervention to reduce overuse of CS in various settings in LMICs and on approaches to overcome barriers to implementation. Our project will go beyond the state of the art for the following reasons. First, it will provide an exhaustive description of the barriers and facilitators to implementing the four components of the QUALI-DEC intervention in various settings under a rigorous formative research phase [19]. This information will help identify and systematically structure-specific determinants associated with implementation success. This is particularly true for the implementation of companionship during labor and evidence-based clinical practice guidelines combined with A&F and opinion leaders. Second, it will help explain what influences implementation outcomes and provide information on the overuse of CS in settings where the performance in terms of CS decision-making is currently undocumented. Third, it will integrate qualitative and quantitative data to strengthen the internal validity of the results. Combining the merits of multiple theoretical approaches, the QUALI-DEC project will offer a more complete understanding by providing a theory of change that could be adapted to different settings [29]. Fourth, it will analyze the scalability and transferability of the intervention to other contexts, a pressing issue considering the global rise in CS in the past few decades. Importantly, QUALI-DEC focuses on LMICs, where addressing the challenge of overuse has become a priority.

In conclusion, the findings from this pragmatic evaluation will be highly applicable to practitioners, service managers, and policy-makers who are tasked with implementing a nonclinical intervention to reduce unnecessary CS in LMICs. In addition, the findings will determine the effectiveness and cost-effectiveness of an innovative implementation strategy tailored to the needs of the local setting. This strategy aims to implement four active components that are expected to improve quality decision-making for the mode of birth so that only the women who need to have a CS undergo the procedure. The strategy will involve women, healthcare professionals, and organizations and will focus on how to best and most effectively implement these components, considering the local needs and resources in each country. Overall, our project will improve the appropriate use of CS and address several sustainable development goal targets, including improving maternal and neonatal health and reducing inequalities within and between countries.

